## Abstract

**Introduction:**

Hospital-at-Home interventions have been shown to be clinically and cost-effective, and many healthcare systems internationally are investing in scaling-up such interventions. However, most existing studies focus on how effective the intervention is, rather than how to successfully scale it up. We report a study protocol for a theory-driven investigation of a Hospital-at-Home intervention. We propose a novel combination of two established implementation science frameworks—the EPIS framework and the Scale-Up framework—and apply it to a planned scale-up of a Hospital-at-Home intervention in Singapore.

**Methods:**

and analysis: This will be an observational cohort study across 23 months (May 2022 to April 2024) to evaluate the association of outer and inner contextual factors on key implementation outcomes—the volume of patients admitted, operational efficiency and levels of adoption. Statistical process control graphs will be used to examine variation in the implementation outcomes over time. Linear regression will be applied to assess associations of outcomes with contextual factors that are continuous variables; logistic regression will be applied to assess the associations of outcomes with binary/descriptive contextual factors. To supplement these, qualitative methods will be applied using a content analysis of monthly meeting minutes and focus group discussions with the implementation team to understand and explain the outcomes of the observational cohort study.

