### Measurements and outcomes

The primary implementation outcomes—defined as ‘the effects of deliberate and purposive actions to implement new treatments […] and are distinct from service and client (patient) outcomes’ (22)—of the scale-up process are as follows:
1.Volume: number of patient admissions to NUHS@Home and associated bed days per month2.Operational efficiency: bed occupancy rate of NUHS@Home, defined as the number of bed days occupied/virtual bed capacity * number of days that month3.Adoption: proportion of patients admitted to NUHS@Home/total patients admitted to affiliated hospital wards for established clinical pathways. Within the NUHS setting, these currently include: cellulitis, urinary tract infections, gastroenteritis, dengue fever, and exertional rhabdomyolysis, but may increase with the development of new clinical pathways.Relevant clinical outcomes will include the rate of unplanned returns to hospital, 30-day readmission rate, HaH mortality rate, and rate of patient safety incidents. At the initial set-up of the NUHS@Home service, our team developed a list of patient safety indicators by reviewing inpatient hospital reporting guidelines and adapting them for NUHS@Home. These indicators include: (1) diagnosis, treatment and procedure-related complications, (2) laboratory medicine and sample-related complications, (3) peripheral venous complication-related complications, (4) medication-related complications, (5) patient falls, (6) pressure injuries, (7) sharps injury and body fluid splash related and (8) staff and visitor incidents. These indicators will be tracked throughout the study period.

In addition, basic patient demographic data (e.g., age, gender) will also be collected to provide descriptive context for the implementation analysis.

A key tenet of implementation theory is that the scale-up process and the associated outcomes of that process (summarized above) will potentially be impacted by, or at least associated with, the context of the implementation. To better understand the impact of context, we applied the EPIS framework to define contextual influences on the outcomes described above and developed a corresponding measurement plan, summarized in Table 3.

**Table 3 T3:** Measurements of contextual influences.

Measurement (per month)	Definition
Implementation outcomes (IO)	
Volume	• Number of patient episodes • Number of bed days
Operational efficiency	• Bed days occupied • Virtual bed capacity

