### Data collection and data sources

Data sources for this study will include chart review from electronic medical records, human resources data, operational data, and standardized questionnaires disseminated to the NUHS@Home Implementation Team. Collected data will be consolidated into data collection forms (DCFs) on a monthly basis (i.e., 23 data points in total) by a study team member (SL). The DCFs are available in the Supplementary Material, and the data collection strategy is summarized in Table 4.

**Table 4 T4:** Data collection strategy.

DCF	Data	Participants	Data sources
DCF 1 (operational data)	• Indicators of volume and utilization • Outcome indicators • Patient satisfaction indicators • Average occupancy rates of referring hospitals • Average number of emergency department lodgers in referring hospitals • Volume of patients in each clinical pathway • Number of home visits conducted	Operations team	Chart review Clinical operations databases Patient satisfaction team
DCF 2 (service structure and organization)	• Source of service funding • Operating and shift hours • NUHS@Home Leadership & Administrative team	Program lead	Operations data
DCF 3 (clinical operations)	• Referral parameters for active clinical pathways • New/modifications in Clinical Guidelines	Clinical service lead	Operations data Chart review
DCF 4 (service development activities)	• Publicity Broadcasts (by hospital leadership) • Publicity Broadcasts (to staff) • Publicity Broadcasts (to patients) • Engagements with external organizations • Quality and Safety Review Process • New/modifications in Policies • Technology Systems Used • Infrastructure change(s) • External Service Vendors	Operations team to draft a response but all leads to review	Operations data
DCF 5 (staffing)	• Operating and shift hours • Clinical organizational staffing • Clinical staff • Staff demographics • Staff training	Clinical, nursing, pharmacy, allied health and operations lead to fill in separately	Operations data Human resources data

DCF, data collection form.

Color coding: implementation outcome, clinical outcome, outer context, inner context.

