### Data analysis

Both implementation and clinical outcomes will be described descriptively over time to contextualize the scale-up process. We will also use statistical process control (SPC) graphs to examine variation in the three defined implementation outcomes over time. To determine the association of different contextual factors with these outcomes, each contextual factor will first be categorized as either continuous (e.g., bed occupancy rates of referring hospitals) or binary/descriptive (e.g., change in funding source). For continuous variables, unadjusted and adjusted linear regression will be used to statistically assess associations between the number of contextual factors and their values and each implementation outcome to determine whether certain contextual factors are more influential than others. For binary/descriptive variables, contextual events will be annotated on the SPC graphs to assess if a clinically significant relationship exists. These analyses will be supplemented with multivariable regression to adjust for potential confounders. This approach has been previously applied in a similar ‘naturalistic’ implementation evaluation of a hospital-based scaled intervention in the UK (25).

Qualitative data from focus group discussions and meeting minutes will be analyzed using Atlas.ti software, guided by Braun and Clarke's thematic analysis approach (26). Chat logs, transcripts, and observations will be coded inductively, i.e., without any theoretical preconceptions, and themes reflecting implementation aspects will be identified and summarized. In the first stage, data will be deconstructed systematically into first-order concepts. In the second construction stage, the concepts previously developed will be reassembled into new patterns and a constant comparison technique will be carried out to compare the incidents applicable to each emerging theme. The third and final stage of analysis will include the confirmation of the conceptualization of the new phenomenon and a descriptive narrative summary will be created using second-order concepts. The analysis will seek to establish whether the emerging theme represents a barrier or a driver. Results from the different methods will be triangulated for the final data analysis.

Interim analyses will be conducted every three months, with feedback provided to the implementation team as needed.

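### The Abstract picks linear or logistic regression by the type of contextual factor rather than by the outcome, and the Data analysis section states a different method for the same factors

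*Protocol article*

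**What the plan says.** The Abstract (Methods) sets a two-branch rule. For one branch, "Linear regression will be applied to assess associations of outcomes with contextual factors that are continuous variables"; for the other, "logistic regression will be applied to assess the associations of outcomes with binary/descriptive contextual factors".

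Measurements and outcomes defines the three implementation outcomes:

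- volume, the "number of patient admissions to NUHS@Home and associated bed days per month";
- operational efficiency, the "bed occupancy rate of NUHS@Home, defined as the number of bed days occupied/virtual bed capacity * number of days that month";
- adoption, the "proportion of patients admitted to NUHS@Home/total patients admitted to affiliated hospital wards for established clinical pathways".

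Under Data collection and data sources, the data are consolidated "on a monthly basis (i.e., 23 data points in total". Ethics and dissemination adds that no data on individual patients will be collected.

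Data analysis also starts by sorting each factor as continuous or binary/descriptive. Continuous factors get unadjusted and adjusted linear regression. For the others, "For binary/descriptive variables, contextual events will be annotated on the SPC graphs to assess if a clinically significant relationship exists". The next sentence says that multivariable regression will supplement these analyses to deal with confounding. Its type is not named, and the word logistic does not appear in that section.

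**The concern.** The scale of the dependent variable decides between linear, logistic and count regression. The scale of a predictor does not: a 0/1 factor is an ordinary covariate in any of them. The Abstract turns this round. Read literally, it calls for logistic regression of outcomes that are not binary. That would need either a cut-point on the outcome, which is nowhere declared, or the contextual event as the dependent variable, which reverses the study question.

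The two sections also name different methods for the same factors. One would give odds ratios; the other gives a judgement from a chart, followed by an unspecified regression. Data analysis wants to learn whether some contextual factors are more influential than others. That comparison is not possible if one class of factor is reported as linear coefficients and the other as odds ratios or chart marks.

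**Working it through.** No sample size, power or alpha figure is attached to this point, so there is no plan figure to reproduce. The check is a comparison of the sections, with a small illustration.

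**1. Scale of each outcome at the monthly unit**

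| Outcome | Scale | Binary? |
|---|---|---|
| Admissions, bed days | count | no |
| Occupancy | ratio of bed days used to bed days available | no |
| Adoption | numerator over denominator | no; a grouped proportion |

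The clinical outcomes do not supply a binary variable either: they are monthly rates and are only described over time. Without patient-level data there is no individual 0/1 record to model.

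**2. Can logistic regression be fitted to volume?** The log-likelihood contribution of an observation y is y·log(p) + (1 − y)·log(1 − p), which needs y between 0 and 1. The Sample size section anticipates 1,012 patients over 23 months, so a typical month has 1,012 / 23 = 44. Putting y = 44 in gives 44·log(p) − 43·log(1 − p), which grows without limit as p approaches 1. There is no estimate.

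**3. Illustration on assumed data.** 23 months, with one 0/1 factor switching on from the 12th (11 months off, 12 on).

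- Volume: Poisson counts with mean 30 before and 55 after, a simulated shift of 25. Least squares gave an intercept of 29.5 and a slope of 25.1.
- Occupancy: mean 0.60 before and 0.75 after, SD 0.08, a simulated shift of 0.15. Least squares gave a slope of 0.18.
- Logistic regression of the same counts stopped with an error, because the response lay outside the unit interval.

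A binary predictor is therefore no reason to leave linear regression, and logistic regression does not run on volume as defined.

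**4. Where logistic regression would fit.** Table 3 records, per pathway, patients admitted to NUHS@Home and patients admitted to the affiliated wards. These counts can form a grouped binomial response, provided the number of trials includes the home admissions. The reason would be the outcome's scale, so the model would apply to continuous and binary factors equally.

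**5. How many factors are affected.** Table 3 lists 6 outer-context and 7 inner-context domains, 6 + 7 = 13. By my reading, at least six contain a categorical or event-type measure: funding (source), organizational characteristics (structural changes), leadership (team components), quality and fidelity (policies, technology systems), staffing (training programs, referral hours) and infrastructure (structure of command center and support services).

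**6. The two sections side by side**

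| Factor type | Abstract | Data analysis |
|---|---|---|
| Continuous | linear regression | linear regression, unadjusted and adjusted |
| Binary/descriptive | logistic regression | SPC annotation, then multivariable regression of unnamed type |

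The first row agrees and the second does not.

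**The case against.** The strongest reply is that the Abstract clause is a slip, that Data analysis is the operative text, and that Data analysis does not plan logistic regression at all. The study calls itself descriptive, sets no sample size target, claims associations only, and explains its results with qualitative work. An article may also leave the exact model to a fuller plan. Much of this stands, and it bears on severity. It does not remove the point, because the objection is to a method that is stated wrongly and then contradicted, not to missing detail. Data analysis also keeps the habit of letting predictor type decide the method.

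A second reply is that logistic regression suits adoption. That is true for one outcome of three, but for a reason that the article does not give.

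A reader might go further in three ways that the documents do not support:

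- *Binary factors get no effect estimate.* The multivariable regression that follows the annotation sentence can be read as covering both branches, so this is not established.
- *Logistic regression would often break down through complete separation.* That presumes the event is made the dependent variable, which neither section says, and it needs a monthly trajectory that the article does not give. With volume assumed to rise from 8 to 80 a month, simulations gave anything from about 2% to 46% of series, depending on the assumed trend shape, noise and switch date. No figure can be attached.
- *Constant-variance errors are wrong by a factor of 25/3, about eight.* This assumes a start at 3 beds inside the study window. Table 1 gives 3 beds for set-up and 25 for the next phase, and data collection begins with that next phase. Monthly capacity within the window is not stated. Linear regression on monthly aggregates is a common approximation, and robust errors can deal with unequal variance.

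**Conclusion.** The point holds as an error in a stated rule and a contradiction between two sections. The Abstract chooses the regression by the wrong variable, and as written its logistic branch cannot be fitted to volume and is justified only for adoption, on other grounds. Data analysis gives a different method for the same factors. The size is one of scope rather than a number: three implementation outcomes, none binary by month, and at least 6 of 13 contextual domains with factors on the affected branch, the latter resting on my classification of Table 3. The conclusion assumes that the month is the unit of analysis, as the data collection section states. It does not depend on the simulated values. This should be fixed; the operative section's omission of logistic regression and the study's descriptive aims keep it from being more serious.

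**What to change.** Remove the rule that ties method to predictor type from the Abstract and from Data analysis, and make the two agree. Then state one model per outcome, chosen by its scale, for example:

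- volume: a count model, or linear regression with robust errors;
- occupancy: linear or fractional regression;
- adoption: grouped binomial regression allowing for overdispersion.

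Enter binary contextual events as dated 0/1 terms in the same model as the continuous factors and time, so that both classes are estimated on one scale for each outcome. With 23 monthly points only a few terms can go in together, so the factors will need an order of priority. Keep the SPC annotation as illustration.

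The cost is rewording in two places and ordinary analysis work in standard software. No new data are needed: the monthly forms already record the counts, capacities and contextual events.

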**Ethics and dissemination:**

This protocol has been reviewed and approved by the National Health Group Domain Specific Review Board: Reference Number: 2023/00245. Apart from the end-of-study focus group discussions, waiver of informed consent was sought as the data sources were a review of routinely collected retrospective data. The results of this study will be disseminated to peer-reviewed journals, presented at conferences and shared with policy-level stakeholders.

## Introduction

In many health systems, the demand for hospital beds driven by ageing populations is increasing faster than the available supply. As a result, sustainable and effective alternatives to hospitalization are becoming increasingly important. One such strategy is the Hospital-at-Home (HaH) service, which substitutes traditional inpatient care with treatment delivered in the patient's home (1). HaH is a complex intervention providing hospital-level services at home that involves a daily “ward round” via virtual or home visits, administration of intravenous therapy, and simple investigations at home, with 24/7 access to the care team. These services can be technology-enabled, utilizing remote monitoring and telecommunication systems. Across multiple randomized controlled trials conducted in Australia, Europe, and the USA, HaH interventions have demonstrated similar or improved clinical outcomes and positive patient experiences, often at a lower cost to the healthcare system (2–5).

In recent years, many healthcare systems have invested heavily in the development of HaH programs, including Singapore (Mobile Inpatient Care @ Home) (6), NHS England (Hospital-at-Home/Virtual Wards) (7, 8), and the Center for Medicaid and Medicare Services (Hospital-at-Home) in the United States (9). Although a number of studies have addressed implementation (10, 11), most ongoing evaluations remain focused on safety, efficacy, and cost-effectiveness (2, 3). Despite generally positive results, many pilot programs struggle to scale from a census of 3–5 patients per day to 50–100 patients. Apart from limitations in operational models, we believe that a limited understanding of implementation factors and the lack of systematic application of implementation science concepts (as opposed to intuitive ‘trial and error’) account for at least part of the lack of why scalable HaH models remain elusive globally.

In this protocol, we report a retrospective study of the planned scale-up of a HaH program in Singapore, from its pilot phase to full scale implementation. Our aim is to gain insights into barriers and facilitators influencing the scale-up process of HaH services. The primary aim is to apply well-established implementation research concepts to a HaH scale-up process to understand the barriers and drivers of the process and the associations with implementation success (or failure). Our overarching question is: How do we scale up HaH successfully?

## Methods and analysis

### The intervention, NUHS@Home

NUHS@Home is the HaH service of the National University Health System (NUHS), an academic health system in Western Singapore (12). The NUHS comprises two emergency departments, one urgent care center, three acute hospitals, three national specialist centers (cancer, cardiology and transplant), and a network of primary care clinics (including government-funded polyclinics and private general practitioner clinics as part of a primary care network).

With preliminary studies showing demand and interest from patients and providers (13, 14), NUHS@Home started was launched in September 2020 as a small-scale pilot to test the feasibility of the care model. In the pilot, multi-disciplinary care teams delivered inpatient-level care to patients at home, aligned with international HaH programs. NUHS@Home adopts an inpatient acute bed substitution approach, led by a consultant specializing in general/acute medicine. Key features of care include: (1) daily virtual ward rounds by doctors followed by home visits if physical reviews are indicated; (2) home visits by nurses and allied health professionals for procedures (e.g., intravenous medication or venipuncture) or therapy; (3) remote vital signs monitoring, and (4) a round-the-clock hotline to the care team.

Evaluation of this one-year pilot, operating with a virtual capacity of 3 beds and caring for 108 patient episodes, demonstrated that acute care at home is feasible, safe, and effective (15). From September 2021, due to the COVID-19 surge, NUHS@Home rapidly scaled to over 100 virtual beds, delivering protocolized COVID-19 care to over 2,000 patient episodes (16). Although COVID-19 service demands and patient acuity are lower and not representative of typical patients admitted to HaH programs, insights gained during this period were useful for plans for further growth.

The success of the pilot helped drive financial, regulatory, and policy shifts to support HaH scale-up nationally. The Ministry of Health launched a 2-year “sandbox” from 2022 to 2024 to support and finance these efforts. With this sandbox, patients admitted to HaH programs are eligible for subsidies similar to traditional inpatient care, with an aim to eventually transition to mainstream healthcare delivery (6). As such, NUHS@Home has planned for major expansion from 3 to 50–100 virtual beds within 3–5 years.

This protocol focuses on the evaluation of the scale-up of NUHS@Home, aiming to identify barriers and facilitators to the successful expansion of the HaH services.

### Implementation frameworks

This evaluation will combine two established implementation frameworks—the Exploration, Preparation, Implementation, Sustainment (EPIS) Framework (17, 18) and the Scale-Up Framework (19).

EPIS provides a useful macro-framework for analyzing implementation processes. It outlines four key phases—Exploration, Preparation, Implementation, and Sustainment—and identifies contextual influences across each phase. Contextual influences, defined as factors external to the intervention itself (20), may be further classified into outer context (i.e., healthcare system) and inner context (i.e., local organizational aspects). Examples of these influences include elements of leadership (within and outside the NUHS@Home team and NUHS), characteristics of the local patient population, fidelity of implementation (i.e., implementing NUHS@Home as originally designed), workforce characteristics, and more. In the field of implementation science, contextual factors have consistently been identified as key to the success or failure of implementing evidence-based interventions (21), even more than the quality and nature of supporting evidence or the complexity of the implementation process. These contextual influences are therefore the primary focus for our research and evaluation. Furthermore, EPIS offers a (chrono)logical lens through which the process of implementation can be studied as it takes place and evolves. This is useful and applicable as we study the scale-up process *in situ*, i.e., as it happens within the NUHS setting.

The macro approach of EPIS is complemented by an action-orientated framework to define and operationalize the specific elements of the scale-up process. This is a critically important aspect of the research, as it will lead to the ultimate ‘manualization’ of the scale-up process to create generalizable findings. The Scale-Up framework offers precisely this, in an ideal complement to EPIS. The Scale-Up framework breaks down scaling-up into 4 phases: (1) set-up, (2) develop the scalable unit, (3) test of scale-up, and (4) go to full-scale (Figure 1). Table 1 maps out the growth of NUHS@Home following these phases. The focus of our research is to study the process of developing a scalable unit (phase 2) and test of scale-up (phase 3).

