### Study design

This is a retrospective observational cohort study to evaluate implementation outcomes using the EPIS framework during the planned scale-up of NUHS@Home over 23 months. The primary methodology will be quantitative in approach, supported by an explanatory qualitative study with the implementation team to understand which factors are associated with the assessed implementation outcomes and how. The period of data collection will begin with the transition to phase 2 (‘develop the scalable unit’), between May 2022 to April 2024.

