## Discussion

This study aims to deepen our understanding of how to effectively scale up HaH interventions, which hold significant promise in addressing critical challenges in healthcare systems. Large-scale HaH programs may reduce the demand for expanding or constructing new hospitals, curb rising healthcare costs, and shift care towards more patient-centered, home-based care models.

A key emphasis of this study is the adoption of a systematic theory-driven approach to evaluating the scale-up process, with a focus on identifying both barriers and facilitators to full-scale implementation. In doing so, the study contributes to the growing body of HaH literature, aligning with current discourse that moves beyond assessing efficacy alone and toward understanding large-scale adoption strategies.

To our knowledge, this is the first study to integrate two established implementation science frameworks—the EPIS framework and the Scale-Up framework—to analyze the scaling process of HaH interventions. This integrated approach allows for a comprehensive analysis of both the process and the contextual drivers of success or failure associated with scaling. Moreover, the study design was developed in collaboration with key implementation stakeholders from the outset, ensuring practical relevance and robust assessment of real-world conditions.

Nonetheless, there are limitations. This is an observational study treating the scale-up process as a natural experiment. As such, the evaluation is based on the service as implemented, without a control group, which restricts the ability to draw causal inferences. Consequently, the findings are limited to identifying associations rather than establishing definitive causal relationships.

Although a formal cost analysis is not included in this study, we recognize that economic viability is central to the successful scale-up and long-term sustainability of HaH services. A future follow-up economic evaluation study can be conducted to assess the cost implications and potential savings of HaH compared to conventional inpatient care, to inform healthcare financing strategies and policy decisions.

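### The stated research focus includes phase 3 (50–100 beds), but by the protocol's own Table 1 the data window can cover at most four months of it

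*Protocol article*

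**What the plan says.** The section Implementation frameworks sets the scope in one sentence: "The focus of our research is to study the process of developing a scalable unit (phase 2) and test of scale-up (phase 3"). Table 1, in the same section, gives each phase a span of years and a bed capacity: set-up 2020–2022 with 3 beds, phase 2 2022–2024 with 25 beds, phase 3 2024–2025 with 50–100 beds, and full scale 2025–2030 with 300 beds.

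Study design fixes the window: "The period of data collection will begin with the transition to phase 2 (‘develop the scalable unit’), between May 2022 to April 2024". Data collection and data sources adds that the forms are completed "on a monthly basis (i.e., 23 data points in total").

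Three other places touch on larger scale. The Introduction describes "a retrospective study of the planned scale-up of a HaH program in Singapore, from its pilot phase to full scale implementation". The description of the intervention says that "NUHS@Home has planned for major expansion from 3 to 50–100 virtual beds within 3–5 years". The Discussion describes a systematic evaluation "with a focus on identifying both barriers and facilitators to full-scale implementation".

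**The concern.** The scope sentence gives the study two objects, phase 2 and phase 3. The window begins with the first and closes in the year in which Table 1 has the second begin. Nothing in the article says that phase 3 started early or that collection continues into it.

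The Introduction motivates the work by the difficulty of moving pilot programmes from a handful of patients to 50–100, and Implementation frameworks expects the research to lead to a manual of the scale-up process with generalizable findings. If contextual factors associated with volume, occupancy and adoption are estimated almost wholly at or below 25 beds, a reader who relies on the scope sentence would take them as evidence on operation at 50–100 beds. Staffing, vendor or referral constraints may differ there, and these data could not show whether they do.

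**Working it through.** **Inputs.** Window: May 2022 to April 2024 (Abstract, Study design). Phase years and capacities: Table 1. Stated length: 23 months (Study design, Data collection and data sources). Pilot throughput: 8–10 episodes per month on 3 beds; expected volume: 1,012 patients over 23 months (Sample size).

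**1. Length of the window.** Counting both end months: (2024 − 2022) × 12 + (4 − 5) + 1 = 24. The stated 23 is reached only if one end month is left out. That mismatch is a separate matter; both counts are carried below.

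**2. Overlap with phase 3.** Table 1 gives calendar years only, so phase 3 can start no earlier than January 2024.
- May to December 2022 is 8 months and 2023 is 12 months: 8 + 12 = 20 months before any possible phase 3 date.
- January to April 2024 is 4 months. Because phase 2 also runs into 2024, the overlap is anywhere from 0 to 4 months.
- Share of the window: at most 4/24 = 16.7%. With 23 months it is 4/23 = 17.4% if May 2022 is the month left out, or 3/23 = 13.0% if April 2024 is. The upper bound is about 17% either way.

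**3. Overlap with full scale.** 2025–2030 begins after April 2024, so 0 months.

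**4. Capacity.** Phase 2's planned 25 beds are 25/100 = 25% to 25/50 = 50% of the phase 3 range.

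**5. Cross-check against the expected volume.** This assumes that pilot throughput per bed carries over; the protocol does not say so and does not show how 1,012 was derived.
- 1,012/23 = 44 episodes per month.
- Throughput per bed: 8/3 = 2.67 to 10/3 = 3.33 episodes per bed-month.
- Implied mean capacity: 44/3.33 = 13.2 to 44/2.67 = 16.5 beds.
- A straight-line rise from 3 to 25 beds has a mean of 14 beds and gives 14 × 2.67 × 23 = 859 to 14 × 3.33 × 23 = 1,073 episodes, which brackets 1,012.
- A straight-line rise from 3 to 50 beds has a mean of 26.5 beds and gives 1,625 to 2,032, well above it.

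The expected volume fits a study of growth from 3 to 25 beds.

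**6. The 3–5-year expansion plan.** The article does not say from when it is counted. From 2022, when the national sandbox began, 50–100 beds would fall in 2025–2027, after the window. From the September 2020 launch it would be 2023–2025. This text does not settle the timing; Table 1 is the only dated statement of the phases.

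**The case against.** **Phase 3 may be partly observed.** Phases 2 and 3 share the year 2024, so a flat statement that 50–100 beds are not observed would go too far. This stands: the supportable wording is little or none, 0 to 4 months.

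**The study does not claim to observe full scale.** A reader might infer such a claim from "from its pilot phase to full scale implementation" in the Introduction. The phrase most naturally describes the planned scale-up of the programme, not the data window. The scope sentence leaves phase 4 out, and the Discussion names full scale as a goal to which there are barriers and facilitators. This also stands, and the point does not rest on full scale.

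**The focus groups come later.** They take place after quantitative collection closes, and three of their four themes are broader than explaining the measured outcomes, so some early phase 3 experience could surface. That is fair, but they supply no monthly phase 3 volume, occupancy or adoption, and the article calls its primary methodology quantitative.

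**Misreporting is not announced.** A reader might infer that results at 3–25 beds will be presented as findings on the test of scale-up. No section says so. However, the limitations in the Discussion restrict findings to associations without restricting them by phase or capacity, so nothing guards against it.

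**Possible repairs elsewhere.** The COVID-19 surge to over 100 beds began in September 2021, before the window, and the protocol calls those patients unrepresentative. An extension of the study period is foreseen only if a sample size becomes necessary, not in order to reach phase 3.

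**It is only wording.** No outcome, model or estimate changes. True, but the sentence determines what the study may conclude.

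**Conclusion.** The point holds for phase 3. The scope sentence gives the study a property that its window does not provide: at most 4 monthly data points, about 17% of the window, can fall in phase 3, and possibly none. The quantitative associations will describe growth from about 3 to 25 beds, and conclusions on the test of scale-up would be extrapolation.

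This rests on Table 1's years being the actual phase dates and on April 2024 as the end of collection. The throughput cross-check agrees but is not needed. The point does not extend to a claim that full scale is observed, because the article does not clearly make one.

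**What to change.** - In Implementation frameworks, restrict the research focus and the inferences to phase 2 and, at most, the transition into phase 3.
- State the date, at least the month, of the boundary between phases 2 and 3. Flag any early-2024 months that lie in phase 3 in the monthly series, without drawing phase 3 conclusions from them.
- Add to the limitations in the Discussion that the findings are not shown to extend to 50–100 beds or to full scale.
- Keep the full-scale wording in the Introduction and Discussion as motivation or planned trajectory, but not as a description of what is observed.

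The cost is a few sentences and one date. The downside is a narrower claim. If phase 3 is truly meant to be studied, the alternative is an amendment that extends data collection into it, which costs time and further data collection.
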